#### 2.9.2 Statistical methods

Data analysis will be conducted by statisticians who are independent of the research team. All analyses are performed via the SPSS software (IBM SPSS Inc., Armonk, NY, USA). An intent-to-treat analysis will be carried out for participants who receive treatment at least once. Missing data will be imputed in accordance with the principle of multiple imputations. Continuous variables will be imputed using linear regression models, while categorical variables will be imputed using logistic regression models. Multiple imputation was performed with a user-defined number of MCMC (Markov Chain Monte Carlo) iterations. Per-protocol analysis is limited to participants who strictly adhere to the protocol and complete the trial. All the statistical tests are 2-sided, and differences are considered statistically significant at *P* values less than 0.05.

The safety dataset will also include all patients who received ≥1 dose of the intervention. The primary outcomes will be compared between the two groups via the log-rank test and the Kaplan–Meier method, and superiority will be considered with a 95% confidence interval. The secondary outcomes will be presented as frequencies, means, standard deviations (SDs), medians and ranges. To determine treatment effects, changes in the above outcomes from baseline will be analyzed via ANOVA. Group effects and influencing factors will be analyzed via analysis of covariance or a logistic regression model with covariates including sex, age, concomitant medication and measurements at baseline. Subgroup analyses will not be performed to avoid insufficient statistical power because of the small sample size. Safety will be evaluated through tabulations of AEs and coded based on the Chinese version of the Medical Dictionary for Regulatory Activities (MedDRA). Safety data will be presented with descriptive statistics at baseline, 52 weeks and 104 weeks for each group.

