#### 2.4.4 Discontinuation criteria, adherence and concomitant therapy

Long-term medications for the treatment of underlying diseases, such as high blood pressure, are allowed. Other symptomatic treatments, such as NSAIDs, may be used if the investigators judge that they will not interfere with the assessment of the study drug. We strictly prohibit glucocorticoids, either oral or topical. All concomitant medications should be recorded in the case report form (CRF).

The trial intervention should be stopped in the following circumstances: if serious adverse events (SAEs) occur; if the patient’s condition deteriorates drastically during the trial and it cannot be ruled out that the change is related to the trial, the study should be terminated, and the necessary treatment measures should be taken for the patient; and if patients withdraw their consent.

The duration of the intervention phase and subsequent follow-up in this study are notably extensive, particularly for participants who are asymptomatic. To improve medication adherence, our approaches encompass the following aspects:

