#### 2.5.2 The primary outcome

The primary outcome is the time to the occurrence of RA. It is defined as the time interval from inclusion to the occurrence of RA. RA occurrence refers to the confirmation of arthritis or synovitis by ultrasound and meeting the 2010 ACR/EULAR RA classification criteria.

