### 2.6 Participant timeline

Fifty-two weeks of medical intervention will be followed by another 52 weeks of observation, for a total of 104 weeks. The time points for the measurements are as follows: screening (0 days), 4 ± 3 days, 12 ± 5 days, 24 ± 5 days, 52 ± 5 days, 78 ± 5 days and 104 ± 5 days. During the trial and follow-up, participants will be observed and evaluated via clinical and/or imaging examinations.

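### The per-protocol set requires completing the trial with no exception for participants who reach RA, so it can drop primary events; the set called intent-to-treat is a treated-only set

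*Protocol article*

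**What the plan says.** Section 2.9.2 of the protocol article names three analysis sets.

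- Per-protocol: "Per-protocol analysis is limited to participants who strictly adhere to the protocol and complete the trial".
- Intent-to-treat: "An intent-to-treat analysis will be carried out for participants who receive treatment at least once".
- Safety: "The safety dataset will also include all patients who received ≥1 dose of the intervention".

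The primary outcome (section 2.5.2) is a time to event: "It is defined as the time interval from inclusion to the occurrence of RA". Section 2.9.2 analyses it as follows: "The primary outcomes will be compared between the two groups via the log-rank test and the Kaplan–Meier method". Section 2.6 sets the length of the trial: "Fifty-two weeks of medical intervention will be followed by another 52 weeks of observation, for a total of 104 weeks".

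Two provisions of section 2.4.4 bear on who can stay in the per-protocol set. One covers drastic deterioration where a relation to the trial cannot be excluded; in that case "the study should be terminated, and the necessary treatment measures should be taken for the patient". The other is a ban on a drug class: "We strictly prohibit glucocorticoids, either oral or topical".

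**The concern.** In a time-to-event analysis a participant has contributed everything to the primary outcome once RA is confirmed. The per-protocol rule nevertheless asks what happened afterwards: whether the participant stayed to the end and kept strictly to the protocol. A participant diagnosed at week 24 who then leaves, or who is given a glucocorticoid, can be excluded because of the very event being counted. Membership of the set can then depend on the outcome.

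At stake are the number of events in an analysis that starts with few and, if exclusion after RA differs by arm, the direction of the result.

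Two smaller matters belong with this. The set called intent-to-treat is not all randomised participants; it applies the same one-dose criterion as the safety set. And the list in section 2.4.4 opens with stopping the intervention but then speaks of terminating the study, so it is unclear whether outcome visits continue after the granules stop.

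**Working it through.** **Inputs.** Section 2.7: RA incidence 20.0% (FA) and 37.5% (placebo); 30 per group, 72 in total after a 20% addition. Section 2.8: 1:1 allocation.

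**The plan's own size.** The printed formula gives (1.96 + 0.84)² × [0.20 × 0.80 + 0.375 × 0.625] / (0.175 + 0.15)² = 7.84 × 0.394375 / 0.105625 = 29.3, so 30 per group. The article gives no value for ε; 0.175 is assumed as the difference between the two rates. Then 30 × 1.2 = 36 per group, 72 in total. This is reproduced only to fix n = 36 per arm.

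**Formulas.** For an arm with n participants, incidence p and an assumed share f of RA cases excluded:

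- events kept = n·p·(1 − f)
- set size = n − n·p·f
- proportion r = events kept / set size
- implied hazard ratio = ln(1 − r_FA) / ln(1 − r_placebo), assuming proportional hazards and common follow-up
- approximate log-rank power (Schoenfeld, two-sided 5%) = Φ(√D × |ln HR| / 2 − 1.96), where D is total events

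**No exclusion.** Events 36 × 0.20 + 36 × 0.375 = 7.2 + 13.5 = 20.7. HR = ln(0.80) / ln(0.625) = 0.47.

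**Half of RA cases excluded in each arm.** FA: 3.6 / 32.4 = 11.1%. Placebo: 6.75 / 29.25 = 23.1%. Events 3.6 + 6.75 = 10.35, or 10.4. HR = ln(0.889) / ln(0.769) = 0.45.

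Equal exclusion, 36 per arm:

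| Share excluded | FA | Placebo | Events | HR | Power |
|---|---|---|---|---|---|
| 0 | 20.0% | 37.5% | 20.7 | 0.47 | 40% |
| 0.25 | 15.8% | 31.0% | 15.5 | 0.46 | 33% |
| 0.50 | 11.1% | 23.1% | 10.4 | 0.45 | 25% |
| 0.75 | 5.9% | 13.0% | 5.2 | 0.43 | 16% |
| 1 | 0% | 0% | 0 | not defined | none |

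With 30 per arm, events run from 17.25 (no exclusion) through 8.6 (half) to 0 (all).

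**Unequal exclusion.** The documents give no basis for any split; 75% against 25% is an illustration.

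| Excluded, FA / placebo | HR at 20% vs 37.5% (0.47 with no exclusion) | HR if both arms have 37.5% (1.00 with no exclusion) |
|---|---|---|
| 75% / 25% | 0.16 | 0.38 |
| 25% / 75% | 1.23 | 2.66 |

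For the first row: FA 1.8 / 30.6 = 5.9%, placebo 10.125 / 32.625 = 31.0%, and ln(0.941) / ln(0.690) = 0.16.

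**The other two sets.** The stated criteria for the intent-to-treat and safety sets are the same: at least one dose. Section 2.8 has treatment begin immediately after allocation, under blinding, so few never-treated participants are to be expected.

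**The case against.** The best defence is that nothing in the article says RA cases leave. RA is not among the listed reasons for stopping, and Table 2 schedules joint counts, DAS28-CRP, radiography and ultrasound to week 104 with no stop at diagnosis. Completing the trial is not defined and could be meant to include reaching the endpoint. This stands. It makes the loss conditional and its size unknown, but it does not supply the missing exception.

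It can also be said that per-protocol details belong in an analysis plan that is not shown. That would answer an omission. Here the article states a definition, and as worded it does not suit the endpoint.

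A reader might infer three stronger things, none of which the documents support.

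- *That the per-protocol result will under-count RA and shrink the effect.* The absolute difference does fall from 17.5 to 12.0 points when half the cases are excluded. But the planned analysis is a log-rank comparison, and under equal exclusion the hazard ratio barely changes, moving slightly further from 1. The cost is then precision. Bias needs unequal loss, which no passage indicates.
- *That section 2.4.4 removes worsening participants just before ultrasound confirmation.* The clause needs both drastic deterioration and a possible relation to the trial, and it sits in a list governed by stopping the intervention. Ending follow-up is one reading of loose wording. If it were the right one, it would touch every analysis set, not only this one.
- *That the intent-to-treat definition biases the main comparison.* With blinded treatment starting straight after allocation, the effect is probably small.

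**Conclusion.** The point holds in conditional form. As written, per-protocol membership can depend on the primary outcome, because completion and strict adherence are required with no exception for RA. At the plan's rates and 36 per arm, equal exclusion of half the RA cases leaves 10.4 of 20.7 expected events and an implied hazard ratio of about 0.45 instead of 0.47. Unequal exclusion could push the ratio either way. Every excluded share is an assumption, and the figures also assume proportional hazards and no other dropout. The loss disappears if reaching RA counts as completion and later treatment is not a breach, but the article says neither.

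The intent-to-treat label is wrong for a treated-only set, with little expected consequence. The stopping paragraph is ambiguous about follow-up and needs reconciling; no more than that can be drawn from it.

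Severity is moderate to low. The per-protocol analysis appears supportive, although section 2.9.2 does not say which set is primary.

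**What to change.** 1. **Per-protocol set (section 2.9.2).** Judge adherence only up to the earlier of RA or the end of the 52-week treatment period, and count either RA or week 104 as completion. Treatment given after RA is confirmed then does not affect membership. A further option is to drop the completion requirement and censor event-free participants who leave early at their last endpoint assessment; otherwise the set keeps early RA cases but loses early leavers without RA.
2. **Intent-to-treat set (section 2.9.2).** Analyse all randomised participants as randomised, or keep the one-dose rule and call the set modified intent-to-treat.
3. **Stopping paragraph (section 2.4.4).** The sponsor should reconcile the opening words on stopping the intervention with the later words on terminating the study, so that it is clear whether the already scheduled outcome visits continue after granules are stopped. No clinical rule is proposed here.

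The cost is a few sentences and minor extra analysis work: adherence has to be assessed against each participant's RA date. The article reports that recruitment is still under way, so the set definitions can be changed before unblinding.

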### 2.7 Sample size

As this trial primarily assessed feasibility on RA prevention by TCM, sample size was not strictly predetermined. We initially allocated 30 participants per group with an additional 20% potential dropouts, resulting in a total of 72 recruitment. Nevertheless, we provide a formal calculation for reference purposes.

According to previous study (35), we assumed that RA incidence would be 20.0% in the FA group and 37.5% in the placebo group. This allocation ensured an power of over 80%. Calculation was in accordance with the formula of Chow (36) as follow:

$$\text{N}=\frac{{\left({\text{Z}}_{\alpha }+{\text{Z}}_{\beta }\right)}^{2}\,\left[{\text{P}}_{0}\,\left(1-{\text{P}}_{0}\right)+{\text{P}}_{1}\,\left(1-{\text{P}}_{1}\right)\right]}{{\left(\varepsilon +\delta \right)}^{2}}$$

Note: *N* is the sample size of each group. P_0_ and P_1_ are the RA incidence in the FA group and placebo group, respectively. For a two-sided test, α = 0.05, β = 0.2, 1−β = 0.8, Z_α_ = 1.96, Z_β_ = 0.84. The superiority margin δ = 0.15. And ε is the practical margin.

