### 2.8 Randomization and blinding

The randomization will be performed via the block randomization method by using the PROC PLAN procedure of SAS V9.4, which is administered by the Key Unit of Methodology in Clinical Research (KUMCR) at the GPHCM. According to the sample size estimate, 72 patients will be included in this study and randomly divided into two groups at a 1:1 ratio. To avoid wasting random numbers, two extra random numbers were added, and the adjusted random number is 74. Once the sample size reaches 72, patient enrolment will cease, even though there might still be unused random numbers at that point. After informed consent is obtained from participants who meet the eligibility criteria, clinicians can access the online random allocation system to procure the allocation results and immediately implement the intervention measures. When multiple patients are randomly assigned on the same day, the application procedure should be performed one by one. The patients, clinicians and investigators of this trial, including study assistants and statisticians, are blinded to the assignment. Unblinding is permitted in an emergency if a SAE occurs or if the intervention must be known for rescue.

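### Secondary outcomes: the analysis named for treatment effects is an ANOVA of change, usually less precise than the baseline-adjusted ANCOVA that the plan also contains

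*Protocol article*

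**What the plan says.** Section 2.9.2 (Statistical methods) of the protocol article first lists descriptive summaries for the secondary outcomes. It then fixes the inferential method: "To determine treatment effects, changes in the above outcomes from baseline will be analyzed via ANOVA". No covariate is attached to this ANOVA.

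The next sentence reads "Group effects and influencing factors will be analyzed via analysis of covariance or a logistic regression model", continuing "with covariates including sex, age, concomitant medication and measurements at baseline".

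One significance rule covers everything: "All the statistical tests are 2-sided, and differences are considered statistically significant at" P values below 0.05. The article does not call either analysis main or supportive.

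On numbers, section 2.7 states "We initially allocated 30 participants per group with an additional 20% potential dropouts, resulting in a total of 72 recruitment", and section 2.8 says participants are "randomly divided into two groups at a 1:1 ratio".

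**The concern.** In a two-arm trial, the treatment effect and the group effect are the same FA-versus-placebo contrast. The text gives the job of determining it to the change-score ANOVA and puts a baseline-adjusted analysis of the same contrast beside it.

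Two things are at stake:

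- **Precision.** If the ANOVA of change is taken at its word as the treatment-effect analysis, the reported intervals will be wider than they need be for outcomes whose baseline value varies and predicts follow-up only moderately. With about 30 per arm that matters. The article itself avoids subgroup analyses because the sample is small.
- **Choice.** If the two analyses are read as having equal standing, each outcome has two P values for one question, and either could be reported.

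A smaller matter sits in the covariate list. Concomitant medication is recorded throughout the trial (Table 2). If use after randomisation entered the ANCOVA, the adjusted difference would no longer be a clean randomised comparison.

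**Working it through.** **Inputs from the article.** The plan has 30 per group plus 20%: 2 × 30 × 1.2 = 72, as stated, or 36 randomised per arm. Allocation is 1:1 and tests are two-sided at 0.05. The article gives no precision or power figure for the secondary outcomes, so there is none to reproduce. The check uses only the 30 per arm; whether that number suits the primary outcome is a separate question.

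**Assumptions, not in the article.** The baseline/follow-up correlation ρ is 0.3, 0.5 or 0.7. The true effect is 0.5 of the follow-up SD. Baseline and follow-up SDs are equal; this is relaxed in step 3.

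**Step 1: variance.** In units of the squared SD, the per-person variance is 2(1 − ρ) for change and 1 − ρ² for ANCOVA. The ratio of change to ANCOVA is 2/(1 + ρ).

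**Step 2: power.** Power = Φ(0.5 / √(2V/30) − 1.96), where V is the variance from step 1. For example, at ρ = 0.5:

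- Change: V = 1.00, SE = √(2/30) = 0.258, and 0.5/0.258 − 1.96 = −0.02, so power is 49%.
- ANCOVA: V = 0.75, SE = √(1.5/30) = 0.224, and 0.5/0.224 − 1.96 = 0.28, so power is 61%.

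| ρ | V change | V ANCOVA | Ratio | CI wider by | 30 per arm worth, under ANCOVA | Power, change | Power, ANCOVA |
|---|---|---|---|---|---|---|---|
| 0.3 | 1.40 | 0.91 | 1.54 | 24% | 19.5 | 37% | 53% |
| 0.5 | 1.00 | 0.75 | 1.33 | 15% | 22.5 | 49% | 61% |
| 0.7 | 0.60 | 0.51 | 1.18 | 8% | 25.5 | 71% | 77% |

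The interval column is √ratio − 1, and the next column is 30/ratio. If all 36 per arm were analysed, the power pairs would be 43% and 60%, 56% and 69%, and 78% and 84%. The ratios would not change.

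These are large-sample ratios. Simulated null trials with 30 per arm and one baseline covariate gave variance ratios of 1.50, 1.32 and 1.15, so estimating the baseline slope costs ANCOVA little at this size.

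**Step 3: unequal SDs.** With baseline SD s_b and follow-up SD s_f, the ratio is

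1 + (s_b − ρ·s_f)² / [s_f²(1 − ρ²)].

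It is never below 1, and equals 1 when s_b = ρ·s_f. If the baseline SD is half the follow-up SD (assumed), the excess variance is:

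- ρ = 0.3: 0.04/0.91 = 4%
- ρ = 0.5: 0
- ρ = 0.7: 0.04/0.51 = 8%

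**Step 4: two tests of one contrast.** In 20,000 simulated null trials per ρ with 30 per arm, each test alone rejected in 4.8% to 5.2% of trials. At least one of the two rejected in 7.8%, 7.5% and 6.6% of trials for ρ = 0.3, 0.5 and 0.7. They disagreed on significance in 5.6%, 4.7% and 3.4%.

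**The case against.** The best defence is that the baseline-adjusted model is already planned, so precision is not simply discarded. The ANCOVA sentence can also be read as an exploratory companion, and a fuller analysis plan may rank the two. This stands in part. The complaints about precision and about choice are alternatives: if the ANOVA is the designated analysis, the two-test error rate does not arise; if neither is designated, the more precise answer is available. But the article does not merely leave the matter open. Its own words assign treatment effects to the ANOVA, and under either reading one of the two costs remains.

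The size can also be disputed, rightly. Entrants have no synovitis, clinically or on ultrasound (sections 2.3.1 and 2.3.2), so baseline spread in SJC28, and perhaps in other activity measures, will be compressed. Step 3 shows that the loss there can be close to nil. The larger figures are more plausible for VAS, PtGA or antibody titres.

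A reader might infer more than the text supports:

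- **That the ANOVA is run separately at each visit and ignores repeated measurement.** The article says only ANOVA, and a repeated-measures form is not ruled out. Even the absence of covariates is inferred from none being named.
- **That change scores are less efficient at any correlation below 1.** That needs equal SDs.
- **That the treatment estimates are biased.** Under randomisation they are not.
- **That a mixed model over all visits is required.** With about 60 people and floor-bound outcomes it is debatable, and it would have to fit with the planned multiple imputation.

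**Conclusion.** The point holds as a modest, nearly free improvement. The article names, for treatment effects on secondary outcomes, an analysis that in large samples cannot be more precise than the ANCOVA beside it. At equal SDs and correlations of 0.3 to 0.7, the excess variance is 54% down to 18%, and power for a 0.5 SD effect falls by 16 points down to 6 with 30 per arm. The correlations, the equal SDs and the effect size are all assumptions, and for outcomes with little baseline spread the excess may be close to zero. The false-positive figure of 6.6% to 7.8% per outcome applies only if the two tests are treated as unranked.

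The consequence is limited. This is lost efficiency and an unsettled choice in the secondary outcomes of a trial that calls itself a feasibility pilot. The log-rank analysis of the primary outcome is unaffected.

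**What to change.** In section 2.9.2, for continuous secondary outcomes:

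- Replace the ANOVA of change with the ANCOVA already in the plan as the single treatment-effect analysis, adjusted for the baseline value of that outcome, sex and age.
- Report the adjusted arm difference with its 95% CI. Label any ANOVA of change as descriptive or supportive.
- Restrict covariates to values measured at baseline, so that concomitant medication enters, if at all, only as use at baseline.

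Logistic regression stays for binary outcomes, with the same restriction on covariates. A repeated-measures model is optional.

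The cost is about two sentences of wording. The baseline values are already scheduled in Table 2, so no new data are needed. The article describes the trial as still recruiting, so the change can be dated before any unblinded analysis.

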#### 2.5.3 Secondary outcomes

The secondary outcomes include the following:

(1)   Proportions of participants who develop RA at different observation time points.(2)   Autoantibodies: a reduction in anti-CCP or RF titer.(3)   Biochemical tests: the high-sensitivity C-reactive protein (hs-CRP) level and the erythrocyte sedimentation rate (ESR).(4)   Joint symptoms and signs: the 28-tender joint count (TJC28), 28-swollen joint count (SJC28), visual analog scale (VAS) score, morning stiffness, and other complaints, such as pain and numbness.(5)   Systemic symptoms and signs: the Patient’s Global Assessment (PtGA) score, Physician’s Global Assessment (PGA) score, Health Assessment Questionnaire (HAQ) score, and Disease Activity Score in 28 joints-C-reactive Protein (DAS28-CRP).(6)   Generic Quality of Life Inventory-74 (GQOLI-74) score.(7)   Doppler ultrasound of both hands, feet and other affected joints: (A) Mandatory joints: the radiocarpal and midcarpal joints, the distal radioulnar joint, and the 6th compartment; the metacarpophalangeal (MCP) joints in the dorsal position in the second to fifth fingers bilaterally; the proximal interphalangeal (PIP) joints and flexor tendons in the volar position in the second to fifth fingers bilaterally; and the metatarsophalangeal (MTP) joints in the dorsal position in the 2nd to 5th toes in the feet bilaterally. (B) Symptomatic joints: if patients report symptoms in joints other than those described above, the sono-rheumatologist will scan these symptomatic joints at the same time to determine whether there are any sonographic changes associated with synovitis, tenosynovitis, tendinitis, enthesitis or bursitis in these areas (Supplementary Appendix 1).(8)   Digital radiography (DR) of the hands and feet.

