## 4 Discussion

Although previous studies have tested the use of DMARDs to delay the onset of RA (37, 38), there is also a growing need for clinical evidence for TCM.

However, this trial has several potential limitations. It is a small-scale pilot trial, and therefore, the results may not be conclusive or sufficiently generalizable. Nevertheless, any significant differences or trends in the efficacy of FA at the endpoints of this trial will provide seminal evidence for the search for RA prevention, and even neutral results will be important revelations to the community. RA is a serious global rheumatic disease that affects many people both physically and mentally.

With the rapid advances in science and medicine in recent years, remission is no longer the only goal to meet the needs of RA patients. Medical care and management strategies for at-risk individuals are becoming a priority for clinicians and researchers. This trial can provide high-quality data and hopefully suggest a new therapy to prevent rheumatoid arthritis.

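### Two unranked analyses, ANOVA of change and baseline-adjusted ANCOVA, estimate the same treatment effect on the secondary outcomes, and the one assigned to treatment effects is the less precise

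*Protocol article*

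**What the plan says.** Section 2.9.2 (Statistical methods) gives two analyses for the secondary outcomes in consecutive sentences:

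- The first is labelled as the way treatment effects are determined: "changes in the above outcomes from baseline will be analyzed via ANOVA".
- The second follows at once and covers the same outcomes: "Group effects and influencing factors will be analyzed via analysis of covariance or a logistic regression model". The covariates it names are sex, age, other medication in use and the baseline value.

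Nothing in the section says which of the two is the main analysis. One significance rule, with a threshold of 0.05, covers everything: "All the statistical tests are 2-sided, and differences are considered statistically significant at" that threshold.

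Section 2.5.3 lists the secondary outcomes. Table 2 schedules up to six post-baseline visits (weeks 4, 12, 24, 52, 78 and 104). Only the proportion developing RA is tied in section 2.5.3 to several time points. Section 4 (Discussion) calls the trial a small pilot whose results may not be conclusive, then states that "any significant differences or trends in the efficacy of FA at the endpoints of this trial will provide seminal evidence".

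**The concern.** With two randomised groups, the treatment effect and the group effect on a given outcome are one quantity. The plan estimates it twice, by models that can disagree, and gives no rule for which answer is reported as the result.

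Two things are at stake. The first is precision: the sentence that names the treatment-effect analysis names the unadjusted change score, although the baseline-adjusted alternative uses data already collected and has the smaller variance. In a trial planned around 30 evaluable participants per group, that matters. The second is error control: if either analysis may supply a significant result, the error rate per comparison exceeds the nominal 5%. The Discussion's readiness to treat any significant difference or trend as evidence makes the missing ranking more consequential.

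**Working it through.** **Inputs**

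- Group size: 30 per group before the dropout allowance (section 2.7; 60 × 1.2 = 72 in total).
- Significance level: two-sided 0.05 for all tests (section 2.9.2).
- Visits per outcome: Table 2.
- Correlation ρ between baseline and follow-up: not given in the article. Assumed range 0.3 to 0.9.
- The plan states no number of tests or expected chance findings, so there is no figure of its own to reproduce here.

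**Step 1. Precision.** Let σ² be the outcome variance, taken as equal at baseline and follow-up. Per participant, the change score has variance 2(1 − ρ)σ², and ANCOVA has residual variance (1 − ρ²)σ². The ratio ANCOVA / change is (1 − ρ²) / [2(1 − ρ)] = (1 + ρ)/2. The extra participants that the change score needs for equal precision are 2/(1 + ρ) − 1.

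| ρ (assumed) | Variance ratio | Reduction with ANCOVA | Extra participants for change score |
|---|---|---|---|
| 0.3 | 0.65 | 35% | 54% |
| 0.5 | 0.75 | 25% | 33% |
| 0.7 | 0.85 | 15% | 18% |
| 0.9 | 0.95 | 5% | 5% |

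**Step 2. Error from two unranked tests.** Both tests were simulated with no treatment effect: normal data, 30 per group, 4,000 runs per value of ρ.

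| ρ | ANOVA of change | ANCOVA | Either significant |
|---|---|---|---|
| 0.3 | 4.7% | 4.8% | 7.5% |
| 0.5 | 4.9% | 5.2% | 7.6% |
| 0.7 | 4.8% | 5.0% | 6.6% |

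Each test alone holds its level. Taking whichever is significant gives about 6.6% to 7.6%. The simulation standard error of the last column is √(0.07 × 0.93 / 4000) ≈ 0.4 percentage points, so the differences between rows should not be over-read.

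**Step 3. How many comparisons.** The scored outcomes in section 2.5.3 number 13: anti-CCP, RF, hs-CRP, ESR, TJC28, SJC28, VAS, morning stiffness, PtGA, PGA, HAQ, DAS28-CRP and GQOLI-74. In Table 2, 11 of them have six post-baseline visits, anti-CCP has five and GQOLI-74 has four: 11 × 6 + 5 + 4 = 75 outcome-visits. The expected number of chance findings is the number of tests × 0.05, whatever the correlation between tests:

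- one visit per outcome, one analysis: 13 × 0.05 = 0.65
- every visit, one analysis: 75 × 0.05 = 3.75
- every visit, either analysis significant: 75 × 6.6% to 7.6% ≈ 5.0 to 5.7 outcome-visits
- every visit, each test counted separately: 150 × 0.05 = 7.5 nominal hits

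These totals suppose no true effect on any outcome. Under that condition, half of the chance findings would favour FA.

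**The case against.** The strongest reply has four parts.

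**ANCOVA with baseline is already planned.** Precision is therefore lost only if the ANOVA is the result relied on, and at a high correlation the loss is small (5% of variance at ρ = 0.9). This is correct as far as it goes. But the sentence that says how treatment effects will be determined names the ANOVA, so the text points the reader to the weaker analysis.

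**Visit-by-visit testing is not stated.** A reader might infer from Table 2 that every outcome is tested at every visit and that about four chance findings will follow. The documents do not support this. Table 2 is a measurement schedule, and section 2.9.2 does not say whether the ANOVA is run at each visit, at one visit or across visits. The objection stands, and the count has to be given as a conditional range.

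**Key visit, scale and multiplicity belong to an analysis plan that is not shown.** This also stands, and none of these is counted as a defect here. A reader might add that titres and hs-CRP are skewed, or that "Autoantibodies: a reduction in anti-CCP or RF titer" cannot occur in RF-negative participants, whom the inclusion criteria admit. The article gives no distributions, and a numeric titre below a positivity cut-off can still fall, so neither claim is shown.

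**These are secondary outcomes of a declared pilot, with a caveat in the Discussion.** That limits the consequences. It does not settle which of two named models gives the answer, and the same paragraph goes on to treat any significant difference or trend as evidence.

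**Conclusion.** The point holds in a narrow form. Section 2.9.2 fixes two analyses of one treatment effect, ranks neither, and attaches the treatment-effect label to the less precise. This is not a silence for an analysis plan to fill, since the article itself names both methods.

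The precision cost of relying on the ANOVA of change is 5% to 35% of variance in ANCOVA's favour. It rests on equal variances at baseline and follow-up and an assumed ρ of 0.9 down to 0.3. The error per comparison, if either test may be claimed, is about 6.6% to 7.6% instead of 5%, for ρ between 0.3 and 0.7. Expected chance findings range from 0.65 to 7.5, depending on how many visits and analyses are tested, with no true effect assumed.

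A reader might conclude that a false claim of benefit is nearly certain. The documents do not support that: it would need every visit to be tested and the tests to be close to independent. Repeat visits are correlated, and DAS28-CRP overlaps the joint counts and CRP that are listed separately. The primary time-to-RA comparison is unaffected.

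**What to change.** In section 2.9.2, delete the ANOVA of change from baseline. Name one treatment-effect analysis for each continuous secondary outcome: ANCOVA with the baseline value of that outcome as a covariate, or a baseline-adjusted repeated-measures model if several visits are to be used together. Keep logistic regression for binary outcomes such as the proportion with RA, where change from baseline does not apply because no participant has RA at entry. State that secondary results are reported as estimates with 95% confidence intervals and are exploratory, in line with the pilot status given in the Discussion.

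The change needs no new data and no change to visits or sample size. It is a matter of wording and slightly less analysis work, and section 5 says that recruitment is still under way. The downside is that fewer nominally significant results can be claimed.
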